Multiple recent reports [14,15,34,35] suggest the importance for health services research to explore models of organized health delivery that integrate CAM with conventional medicine. Until recently, patients were likely to make decisions about whether to use CAM services without input from allopathic providers [36,37], but today's patients are increasingly "co-managed" by conventional and CAM clinicians. Most patients report using CAM and conventional medicine together and want the opportunity to discuss CAM use with their primary care providers, be respected for their beliefs, and be guided on their use of such treatments [38-40]. Many CAM therapies are used to complement, rather than replace, conventional medicine; therefore, it is important to identify a model that can serve as a unified framework for the decision to use A/C within this context. Thus, we chose a framework to guide our exploration of patients' decisions to use A/C based on a well-accepted model for general health care decision-making and use [41,42], that has been expanded to consider integration of CAM services (see Figure 1)[43]. This model for CAM use includes commonly used self-directed practices and products as well as provider services that are the central focus of this study. Further, the model includes indicators that may "pull" a person toward A/C use (e.g., responsibility for preventive self-care) or "push" patients (e.g., dissatisfaction with conventional medicine)[44,45]. Research on conventional medicine use suggests that enabling factors (e.g., access, information about forms of care) and need (e.g., type and level of impairment) are the primary drivers of health care decisions [46-48], but their relative importance has not been explored for A/C service use.

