## Methods/Design

### Study Overview

The overarching goal of this multi-phase, mixed methods study is to understand the real world implications for patient care and patient satisfaction of acupuncture and/or chiropractic treatment for CMP. Our study setting is a closed patient population HMO in which insurance coverage has been available for A/C treatments. In order to accomplish our goal, we divided our work into three complementary but distinct phases as summarized in Figure 2. Phase 1 involves assembling and exploring a research database with 5 years (2006-2010) of prospectively collected elements available within the HMO. We will identify HMO members who satisfy our study definition of CMP (see Table 1). The database will include members with evidence of using A/C services and a matched comparison group without such evidence. We will then compare these groups on clinical care outcomes and costs derived using EMR data. These analyses will be augmented with patient-reported out-of-plan A/C utilization. Phase 2 includes qualitative methods to describe the characteristics of A/C services received by HMO-based CMP patients and the decision-making processes of allopathic providers and patients in choosing such services; this will allow us to design the appropriate data collection tools and strategies for Phase 3. During Phase 3, we will conduct a longitudinal prospective cohort study of carefully matched samples of A/C and non-A/C patients. Participant selection will rely upon clustering/matching methods identified during Phase 1, refined by Phase 2 qualitative findings, and augmented by additional, direct-assessed patient-report baseline data. Outcomes will include EMR-derived utilization information and patient-reported outcomes. The patient-reported outcomes will cover clinical, psychosocial, quality of life, service utilization, and health care costs over 12 months. We will develop and/or refine these outcomes in the process of Phase 1 data exploration and Phase 2 qualitative research that explores outcomes that are clinically meaningful to conventional and CAM providers and are associated with high levels of patient satisfaction. Finally, we will compare outcomes from this augmented data set to those found during the Phase 1 EMR-only analyses, conducting sensitivity analyses to test the robustness of our findings and transportability of methodology. While phases 1 and 2 can stand alone, in this project they are preparatory to Phase 3, the longitudinal prospective cohort study.

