#### Phase 3: Prospective Cohort Study to Evaluate Outcomes Associated with the Use of A/C Services

To conduct a prospective cohort study of carefully matched A/C and non-A/C patients, we will use clustering and matching methods identified in Phase 1. These matching approaches will be refined by Phase 2 qualitative findings and augmented by additional, directly assessed, patient-reported baseline data. We will follow matched patients to examine outcomes, which will include EMR (service utilization and health care costs) and patient-reported clinical, psychosocial, and QOL outcomes over a one-year prospective timeframe for each patient. We will compare outcomes from the prospective cohort to those found during Phase 1 EMR-only analyses. Specifically, we will conduct the following activities:

1. Set up a weekly surveillance tracking system to identify CMP patients referred for A/C care to allow timely recruitment of these (index) patients and two carefully matched CMP control patients.

2. Coordinate telephone or online assessments for index and comparison patients upon recruitment (baseline; prior to A/C care) and at 1-, 3-, 6-, and 12-month follow-ups.

3. Compare outcomes (clinical and psychosocial/QOL/satisfaction outcomes and health care utilization) and explore health care costs between those receiving A/C and comparison patients not receiving such services, examining relationships between patient characteristics and decisions to use A/C.

4. Conduct comparative and sensitivity analyses between results using methods that rely solely on EMR-derived data (Phase 1) with those supplemented by patient and provider data (Phase 3).

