### Outcome measures and study instruments

The assessment schedule for standardized questionnaires and delineation of EMR-collected outcomes are shown in Table 5. Patient-reported outcomes are measured in a time frame (1-12 months) consistent with many RCTs and other outcome studies of A/C [19,80,81]. Assessment instruments and domains are consistent with the Initiative on Methods, Measurement, and Pain Assessment in Clinical Trials (IMMPACT) recommendations [82,83]. In addition, we include variables representing patient factors influencing the decision to use CAM [43] (Figure 1 plus others identified in Phase 2) to help refine matches of those who do and do not seek A/C.

**Table 5 T5:** Phase 3 Assessment Schedule

	Assessment Month				
	0	1	3	6	12

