**Secondary Outcomes (survey instruments)**					
Overall well-being (Arizona Integrative Outcomes Scale)	√	√	√	√	√
Patient global impression of change		√	√	√	√
Quality of sleep (ISI)	√	√	√	√	√
Work- and activity-related impairment (NHIS questions)	√	√	√	√	√
Depression (PHQ-8)^1^	√	√	√	√	√
Anxiety (GAD-2)^1^	√	√	√	√	√
Quality of Life/health utility index (SF-12)	√	√	√	√	√
Patient satisfaction		√	√		

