#### Secondary outcomes (patient-reported)

a. Global assessment of change. The Patient Global Impression of Change scale (PGIC [88]) will be used to evaluate participants' overall evaluation of the impact of their A/C treatment.

b. Work-related impairment. Three questions about work/disability status and missed work due to CMP will be adapted from the National Health Information Survey (NHIS) [89].

c. Depression severity. Using the Personal Health Questionnaire (PHQ-8) [90,91], we will measure depression severity. The PHQ-8 is established as a valid screener and severity measure for depressive disorders in large clinical studies [90,92-94]. Baseline depression will also be examined as a possible moderator of outcome.

d. Anxiety. The 2-item Generalized Anxiety Disorder Scale (GAD-2) [95,96] will be used to screen for anxiety disorders. The GAD-2 has been used to detect anxiety disorders in primary care and has well established psychometric properties. Baseline GAD-2 scores will also be examined as another possible moderator of outcome.

e. Quality of life/health utility. The SF Health Survey (SF-12v2) [97] will be used to measure quality of life. The SF12 is a widely used and well-validated generic measure of functioning that is a recommended IMMPACT measure for examining functioning (this will also be used as a health utility measure) [82].

f. Patient satisfaction. Finally, participant satisfaction with services provided by the health plan (allopathic providers) (0 = worst health care possible, 10 = best health care possible) will be assessed as well as satisfaction with A/C provider when pertinent [98]. We will also use the practitioner skill subscale from a self-report outcome measure designed for assessing CAM treatments [99,100].

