### Phase 3 Data Analysis

#### Patient-reported outcomes

For the patient-reported outcomes in Phase 3, we will examine differences in baseline measures between participants with and without data at the 1-, 3-, 6-, and 12-month  follow-ups. Variables related to missingness will be included in the main analyses as covariates to reduce bias in the estimates [109,110].

We will use multilevel modeling to examine differences across time in primary (pain intensity/interference/bothersomeness) and secondary patient-reported outcomes between A/C users and matched comparison participants. Two parameters (linear and quadratic slope) will characterize change across time, with linear slope capturing initial rate of change and quadratic slope reflecting the degree to which the change slowed (or increased) over time. Thus, the quadratic model for time (baseline and 1-, 3-, 6-, and 12-month follow-ups) captures nonlinear change across time. Unlike repeated measures analysis of variance, multilevel modeling does not require data at all time points from each subject, so data from all subjects will be included in analyses. Depending upon the distribution, normal, logistic, or Poisson models will be used. Importantly, these analyses can be adjusted using additional information collected from participants during the baseline assessment that we may identify in Phase 2 as influencing A/C decision-making. This will better control for factors not available during comparison patient identification when only EMR data will be available for matching/clustering.

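### Satisfaction with health-plan care has no pre-A/C measurement, so its comparison between A/C and comparison patients is open to confounding by prior satisfaction

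*Protocol article*

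**What the plan says.** - **Outcome.** Item f under Secondary outcomes (patient-reported) defines "participant satisfaction with services provided by the health plan (allopathic providers") on a 0–10 scale. Satisfaction with the A/C provider is collected separately, where it applies.
- **Schedule.** In Table 5 the row "Patient satisfaction" is ticked at months 1 and 3 and is blank at months 0, 6 and 12. The Phase 3 activity list places assessments "upon recruitment (baseline; prior to A/C care) and at 1-, 3-, 6-, and 12-month follow-ups", so month 0 is the only assessment guaranteed to precede A/C.
- **Selection.** The decision framework in the Background says that some indicators may push "patients (e.g., dissatisfaction with conventional medicine") toward A/C.
- **Comparison.** Phase 3 activity 3 is to "Compare outcomes (clinical and psychosocial/QOL/satisfaction outcomes and health care utilization") between those receiving A/C and comparison patients. The Study Overview sets the overarching goal as to "understand the real world implications for patient care and patient satisfaction of acupuncture and/or chiropractic treatment for CMP".
- **Baseline factors.** The section on outcome measures says "we include variables representing patient factors influencing the decision to use CAM", meaning those in Figure 1 plus others found in Phase 2.

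**The concern.** The plan treats satisfaction with conventional care in two roles: as a possible reason for becoming an index patient, and as an outcome compared between index and comparison patients. When a variable plays both roles, a value taken before exposure is what separates a difference that was already there from one that follows A/C. The schedule provides none.

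At stake is the reading of the satisfaction result. If index patients start out less satisfied with the health plan, a lower month-1 or month-3 rating could be taken for an effect of A/C, or could mask a real gain. If they start out more satisfied, for example because a referral pleased them, the error runs the other way. The missing value is also unavailable as a covariate for the other outcomes, although the plan itself names the construct as a decision factor. It cannot be collected once a participant has passed the pre-A/C assessment.

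**Working it through.** No figure in the protocol underlies this point, so there is none to reproduce. The check is a reading of the schedule, followed by an illustration on stated assumptions.

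**Reading**

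1. *Is there a month-0 value?* No. Among the survey outcomes in Table 5, only satisfaction and the global impression of change lack a month-0 tick. Impression of change cannot have a baseline; a 0–10 rating of health-plan care can.
2. *Could patients give one?* Yes. Index patients have an incident A/C referral (Phase 3 participants and recruitment), and comparison patients need a primary care visit within one month of it (Identification of comparison participants). Both groups have recent conventional care to rate.
3. *Is there a substitute?* None is listed. Table 3 (EMR matching variables) has no satisfaction item. Neither do the month-0 patient characteristics in Table 5, nor the factors described under Patient characteristics and potential moderators. The nearest row covers expectations and CAM attitudes, which is a different construct.
4. *Does the planned model help?* The multilevel model for patient-reported outcomes says "Two parameters (linear and quadratic slope) will characterize change across time", starting from baseline. This outcome has no baseline from which change can be described.

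**Illustration**

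Inputs from the protocol: 200 index participants per modality with two comparisons each, so 200 v 400 (Phase 3 Sample Size).

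Inputs assumed, not in the documents: a baseline gap d between groups in SD units; a correlation r between month 0 and follow-up; no A/C effect; equal SDs; full follow-up; a gap that carries forward through the regression on baseline; an unadjusted two-sided test at 0.05.

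- Spurious follow-up difference = d × r.
- Standard error = √(1/200 + 1/400) = √0.0075 = 0.087 SD.
- False-positive probability = Φ(d·r/SE − 1.96) + Φ(−d·r/SE − 1.96).

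| d | r | d × r | (d × r)/SE | Falsely significant |
|---|---|---|---|---|
| 0.1 | 0.3 | 0.03 | 0.35 | 6% |
| 0.1 | 0.5 | 0.05 | 0.58 | 9% |
| 0.2 | 0.5 | 0.10 | 1.15 | 21% |
| 0.3 | 0.6 | 0.18 | 2.08 | 55% |
| 0.4 | 0.7 | 0.28 | 3.23 | 90% |

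A gap of 0.2 to 0.4 SD with r of 0.5 to 0.7 gives 21% to 90% against a nominal 5%. A gap of 0.1 SD with r = 0.3 gives 6%, which is hardly a problem. The table shows how much depends on a quantity the schedule leaves unmeasured.

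**The case against.** The strongest reply is that the questionnaire is deliberately unfinished. Phase 2 is meant to find confounders that the EMR does not hold and to refine the draft Phase 3 instruments. The analysis section allows adjustment for baseline information identified that way, and patient-reported baseline data may also augment the matching. Figure 1 is not shown, Table 5 lists domains rather than items, and a prior-satisfaction question might sit under the row on CAM attitudes. All this is possible, but no passage commits to such an item, and the one row that names satisfaction leaves month 0 blank. The factor is already named in the framework, so it need not wait for Phase 2.

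Other parts of the reply stand, and they rule out stronger readings that a reader might infer:

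- *That the comparison is confounded, or that the study will report a false effect.* The framework says only that dissatisfaction may push patients. Index patients are referred by plan clinicians, so even the direction of a baseline gap is unknown.
- *That prior satisfaction could not be used in matching.* It is absent from the EMR list, but the protocol lets patient-reported baseline data supplement the match, so a collected value could be used.
- *That 21% to 90% is an expected error rate.* The range rests wholly on assumed inputs and ignores both matching and the planned covariates.
- *That the primary pain comparison is compromised.* Pain is measured at month 0. Any remaining effect through prior satisfaction has no estimate.
- *That satisfaction is always first measured after A/C has begun.* Month 1 follows the pre-A/C assessment, but some referred patients may not have started by then.

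**Conclusion.** The point holds for one secondary outcome. Satisfaction with health-plan care has no scheduled pre-A/C value, the plan itself names dissatisfaction as a possible route into A/C, and no listed measure can stand in for it. The between-group comparison is open to confounding by prior satisfaction. The documents do not show that confounding is present, or which way it would run.

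The harm ranges from negligible to serious according to a baseline gap that nobody will be able to inspect under the present schedule. The illustrative 21% to 90% depends on the assumed gap and correlation and on an unadjusted 200 v 400 comparison. This is a cheap improvement to make before enrolment and does not undermine the primary analysis.

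**What to change.** In Table 5, add a month-0 tick for the single 0–10 health-plan satisfaction item, asked of all index and comparison participants at the pre-A/C assessment. Adjust the month-1 and month-3 satisfaction comparisons for it. List it among the baseline decision factors available as covariates for the other outcomes. Keep satisfaction with the A/C provider descriptive, since comparison patients have no counterpart.

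The cost is one extra baseline question, using an item already in the battery. Adjustment for a single item will not remove confounding perfectly if the rating is noisy, but it makes the baseline gap visible and allows most readers' first question about this result to be answered.

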#### Secondary outcomes (health care utilization through EMR and administrative records)

These EMR-based outcome measures were listed in Table 4 as they also form the basis for our Phase 1 outcome analyses.

*Patient characteristics and potential moderators *include factors that may influence decisions to use CAM (see Figure 1)[101] or that have been found to moderate pain-related outcomes [102-104]. These factors might then be used as additional baseline matching variables or covariates to maximize comparability between index- and matched comparison-participants included in the analyses. Demographics include age, gender, race/ethnicity, education, marital status, employment status, income, and income source. Administrative records will identify participants seeking or receiving worker's compensation or other disability payments for their CMP. This will be augmented by a single-item question about disability status of participants on the questionnaire. We will assess general preventive behavior [105,106] by collecting data on self-management behaviors including physical activity practices. In addition, we will assess participants' general expectations of CMP improvement, improvements with A/C treatment [27,31], and how helpful a variety of CAM services and practices (provider- and self-directed) may be [107]. We will measure other characteristics of the participant's pain condition, including age of onset, perceived etiology of CMP, and type(s) of current CMP. Finally, we will collect data on use of other CAM services/products, including any CAM treatment visits not referred through the health plan (e.g., chiropractic and acupuncture, massage therapists, naturopaths) as well as CAM-related self-care practices (e.g., yoga, meditation, tai chi) and products (e.g., dietary supplements).

#### Health care provider measures

a. Allopathic provider characteristics and factors associated with A/C referrals including questions describing general provider characteristics (i.e., gender, specialty type, professional degree, years in practice, and training/expertise in CMP) and A/C referral attitudes, as well as an EMR-based variable reflecting the inclination for a given provider to refer for A/C services (referral rate per CMP patients on panel).

b. A/C provider characteristics and treatment patterns include questions adapted from the A/C-visit data forms developed by Sherman and colleagues [108] and refined during our Phase 2 interviews with the CAM providers. We also have access to data collected by the health plan on CAM-referred services patients receive (e.g., number of sessions; assigned diagnostic, procedure, and treatment [CPT] codes.

### Phase 3 Data Analysis

#### Patient-reported outcomes

For the patient-reported outcomes in Phase 3, we will examine differences in baseline measures between participants with and without data at the 1-, 3-, 6-, and 12-month  follow-ups. Variables related to missingness will be included in the main analyses as covariates to reduce bias in the estimates [109,110].

We will use multilevel modeling to examine differences across time in primary (pain intensity/interference/bothersomeness) and secondary patient-reported outcomes between A/C users and matched comparison participants. Two parameters (linear and quadratic slope) will characterize change across time, with linear slope capturing initial rate of change and quadratic slope reflecting the degree to which the change slowed (or increased) over time. Thus, the quadratic model for time (baseline and 1-, 3-, 6-, and 12-month follow-ups) captures nonlinear change across time. Unlike repeated measures analysis of variance, multilevel modeling does not require data at all time points from each subject, so data from all subjects will be included in analyses. Depending upon the distribution, normal, logistic, or Poisson models will be used. Importantly, these analyses can be adjusted using additional information collected from participants during the baseline assessment that we may identify in Phase 2 as influencing A/C decision-making. This will better control for factors not available during comparison patient identification when only EMR data will be available for matching/clustering.

#### EMR-related outcomes

To examine total health care utilization across 12 months, the analysis issues laid out for Phase 1 continue to apply. Using the MCG as the unit of analysis, the conventional statistical methods from Phase 1 continuous measures will be assessed by one-sample location tests and discrete outcomes will be assessed by binomial methods or by ordinal multinomial methods in the case of multiple outcomes. Like Phase 1, MCG characteristics in the Phase 3 sample will be related to A/C effects using the models described above. Implementing the same analytic strategy here as in Phase 1 (i.e., using EMR data alone), we will be able to test directly for the contribution provided by the additional prospective information on patient-and-provider characteristics (e.g., pain severity, self-care behaviors, provider attitudes to A/C referral). We will do so by including patient-supplied variables at the patient level in the analytic model and then introducing random-effects terms for the MCGs to account for within-MCG correlation.

